In contrast, ultrasound visual biofeedback (U-VBF) is growing in popularity as biofeedback tool for children with speech disorders [8]. U-VBF holds several practical advantages over EPG: it is cheaper and does not require individualized equipment. The one-off outlay cost of an ultrasound system that is suitable for speech therapy is approximately $6,000 [9], initial outlay for EPG is similar, but in addition each patient requires an EPG plate costing between $300-$570, not including the dental impression cost [7]. Moreover, while EPG images only tongue-palate contact from the alveolar region to the boundary of the hard and soft palate, U-VBF images from near the tongue tip to the root, with pharyngeal articulations, common in CLP, clearly visible. This makes U-VBF arguably the technique of choice for CLP [10]; yet, it is relatively new to the Speech and Language Therapy clinic. This is because it is only now that ultrasound systems for measuring articulation provide fast enough frame rates at an affordable cost.

A recent study showed that ultrasound can be used to identify all of the CSC described in the instrumental literature and that ultrasound assessment has better reliability than traditional perceptual approaches [11]. However, U-VBF has to our knowledge only been used in one small study with two participants with CLP [12]. In that study the U-VBF treatment was effective for one of the children, aged 6;2, who achieved accurate production of target sounds and generalized them to untreated words. In children with other types of speech sound disorders, U-VBF shows positive outcomes for the majority of children and it is particularly useful for establishing new articulations [8]: an area of particular difficulty in CLP [5]. U-VBF is therefore potentially a useful tool for establishing new articulations in children with CLP. The aim of this study is therefore to assess the feasibility and inform the design of a full-scale RCT of U-VBF for children with cleft speech characteristics. Key objectives and success criteria for proceeding to full trial are given below. If these are met, a full-scale RCT will proceed using a similar design. Questionnaires and focus groups will provide qualitative data from patients and carers. If this points to specific improvements that can be made in the design, and they do not interfere with the aims of the large-scale study, they will be implemented.

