#### Objectives

To determine recruitment and attrition rates.75% of children and their families identified agree to participate.75% of children allocated in each group are retained for the duration of the study.To measure pre-post and follow-up outcome measure completion.75% of outcome measures are completed.To measure within-session outcome measure completion.Data is reported from 75% of intervention sessions.To determine acceptability of randomization to children and their families.75% of children and their families rate randomization as acceptable in a questionnaire.To determine the acceptability of ultrasound visual biofeedback as an assessment tool (both groups) and intervention tool (U-VBF group).75% of children and their families rate ultrasound as an acceptable technique in a questionnaire.Focus group analysis contains more positive than negative themes regarding acceptabilityTo measure adherence to the treatment protocol.75% of sessions reach the minimum dosage of 100 trials in both treatment arms.

In addition to the quantitative objectives measuring acceptability using questionnaires, this data will be validated using focus group interviews with parents and participants who volunteer. The interviews will be analyzed inductively to identify emergent themes and deductively, using the Theoretical Framework of Acceptability [14].

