#### Randomization

Following baseline, the children will be randomized by the Glasgow Clinical Trials Unit in a 1:1 ratio, stratified for age. Children randomized to the control arm will be offered U-VBF at the end of the trial if they still present with CSCs which are candidates for U-VBF for ethical integrity and also because previous studies have shown this improves the acceptability of a randomized trial to families [13].

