### Interventions

Both interventions will be delivered by the cleft palate specialist SLTs in the Royal Hospital for Children in Glasgow. Therapy in both treatment arms will be once per week for six sessions with each session lasting up to 45 min. The number of sessions is pragmatic in nature, reflecting current practice, and is designed to highlight initial response to both interventions. It is likely that some children in both arms of the trial may require further speech intervention in the future (after the follow-up measures are taken), and this will be provided in line with standard practice, which includes further U-VBF. Both interventions will focus on acquisition of new speech sounds. Previous studies of children with non-cleft speech disorders show that a new speech sound can be acquired within one to two sessions [21] of U-VBF for most children but that some children take four to six sessions. Target articulations will be decided individually. Both interventions begin with a pre-practice phase where the aim is to teach the child to approximate the target articulation before they can begin the practice phase where at least 100 repetitions are required for learning and generalization. The dosage of a minimum of 100 trials is set in line with [22] who report a minimum of 60 to 120 trials per session for motor-based treatments. However, we recognize that the literature on dosage required during intervention for CSCs is sparse and that there is much variation reported in the literature on articulation intervention [23]. This dosage will be measured in both interventions. In this pilot we will focus on both the pre-practice phase and the first stage of practice: acquisition of a new sound in simple contexts such as “ta, tea, toe” building to short words such as “tap, team, tore” as this is feasible within six intervention sessions. If children are super-responders (i.e., they quickly retain the new speech sound and are able to produce it in complex contexts) then the protocol will also allow us to measure this. Participants will be discontinued from the intervention if they show any adverse effects to the ultrasound treatment—in rare cases, the ultrasound gel can cause contact dermatitis [24].

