### Within-treatment session outcomes

Previous research suggests that one of the main benefits of U-VBF may be efficiency rather than overall efficacy of treatment [8]. We will therefore measure treatment response during each session, rather than just after the course of treatment. The treating SLTs will therefore audio record short treated, and untreated word lists at every treatment session (t1–t6). From this, we will determine how quickly children achieve a new articulation as a measure of response to treatment. These will be rated at the end of the project by SLTs blinded to group.

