### Analyses and statistical power

We aim to recruit 20 children to each arm of the trial. Recruitment will stop once the target number of participants is recruited and within two years from the beginning of the study. No interim analyses will be performed before all data is collected. Definitive comparisons of the interventions will not be undertaken due to the feasibility nature of the study. Details of patient screening, recruitment, retention, withdrawal, and follow-up will be summarized (see research questions above). Adherence to U-VBF will be measured according to the number of patients who complete the intervention in accordance with the treatment manual. Adherence to treatment dosage will be recorded using an intervention pro-forma in each session where the SLT records a tick mark for each trial (i.e., each time the patient attempts to produce the speech sound in treatment, this should be around 100 for both interventions). All sessions will be audio-recorded (consent permitting) and 20% of sessions will be fidelity checked for dosage and adherence to protocol by the research SLT, blinded to group allocation.

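### The session-data success criterion is one overall percentage, so it can be met with one arm at only 50% of its planned sessions

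*Protocol article*

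**What the plan says.** The protocol article lists its progression thresholds under Objectives. For completion of the within-session outcome measures the threshold is "Data is reported from 75% of intervention sessions". It names no arm and does not say whether the sessions are those planned or those held.

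Two other thresholds in the list do refer to the arms. Retention reads "75% of children allocated in each group are retained for the duration of the study", which fixes both the arm and the denominator. Dosage reads "75% of sessions reach the minimum dosage of 100 trials in both treatment arms".

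The Background section makes these thresholds the trigger for the main trial: "If these are met, a full-scale RCT will proceed using a similar design".

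The data in question are described under Within-treatment session outcomes: "The treating SLTs will therefore audio record short treated, and untreated word lists at every treatment session". That section explains that they will show how fast a child acquires a new articulation, on the ground that the benefit of ultrasound biofeedback may lie in efficiency. The Discussion names quicker acquisition as the hypothesis of the planned full trial.

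**The concern.** Speed of acquisition can be compared in a full trial only if session recordings are usable in both arms. The assessments at baseline, 2 months and 3 months cannot replace them, because they do not show response session by session. The criterion should therefore show that the recordings can be obtained in each arm. A single overall percentage lets a complete arm offset a poor one.

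Uneven recording is a credible risk. The treating therapists make the recordings and are not blinded, and the Discussion accepts that they may prefer one intervention. At stake is a go decision that counts session-level data as feasible when one arm has supplied only half of them.

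**Working it through.** The article states no session count for this criterion, so there is no figure of its own to reproduce. The check is direct counting.

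**Inputs**
- Children: "We aim to recruit 20 children to each arm of the trial" (Analyses and statistical power), with allocation "randomized by the Glasgow Clinical Trials Unit in a 1:1 ratio, stratified for age" (Randomization).
- Sessions: "Therapy in both treatment arms will be once per week for six sessions" (Interventions).
- Thresholds: 75% for session data, retention and dosage (Objectives).

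**1. Overall threshold.** Planned sessions are 20 × 6 = 120 per arm and 2 × 120 = 240 in total. The threshold is 0.75 × 240 = 180.

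**2. Lowest passing arm.** If one arm reports all 120, the other needs 180 − 120 = 60, and 60/120 = 50%. The total is (120 + 60)/240 = 75%, a pass.

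**3. Would another criterion catch it?** Suppose every child stays, all 240 sessions take place and every session reaches 100 practice trials, but the word lists are recorded in only half of one arm's sessions.
- Retention counts children, so it is met.
- Dosage counts practice trials, so it is met.
- The outcome-completion threshold belongs to the pre-post and follow-up measures, so it is unaffected.

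Nothing else in the list detects the gap. In this scenario sessions held equal sessions planned, so the result does not depend on the denominator.

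**4. Away from the boundary (illustration).** Assume true reporting rates of 95% and 60%, 120 sessions held in each arm, and independent sessions. The expected total is 114 + 72 = 186, above 180. With A ~ Bin(120, 0.95) and B ~ Bin(120, 0.60), the overall rule passes with probability P(A + B ≥ 180) ≈ 0.87. A rule applied in each arm passes with P(A ≥ 90) × P(B ≥ 90) ≈ 0.0004. The two rates are assumed. Clustering within child would change the probabilities but not the counts in steps 1 and 2.

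**5. Early drop-out.** Retention at 75% allows 20 − 15 = 5 losses per arm.
- If five per arm leave after session 1, sessions held are 2 × (15 × 6 + 5 × 1) = 190.
- Counting sessions held, 0.75 × 190 = 142.5, so 143 suffice, and 143/240 = 59.6% of those planned.
- Counting sessions planned, 180 of at most 190 are needed, so drop-out counts against the criterion.

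**6. Candidate thresholds within each arm.**
- Sessions held: the 120/60 split of step 2 fails, because 60/120 = 50%. With no drop-out each arm needs 90 of 120. With five leaving after session 1, 95 are held and 0.75 × 95 = 71.25, so 72 are needed.
- Sessions planned: the same drop-out would require 90 of the 95 held, or 94.7%.

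**The case against.** The strongest reply is that the article never says the arms are combined. Two other thresholds, completion of outcome measures and acceptability of randomization, also name no arm, so this criterion is not alone in its form. Reporting by arm might be specified in a fuller document. Part of this stands: it would be wrong to say that all the other criteria are set by arm. But the threshold is a stated progression rule, its plain reading is one percentage over all sessions, and the authors named the arms where retention and dosage were concerned.

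A second reply is that the 50% case is extreme, since it needs one arm complete, and that both arms share the therapist team, the site, the schedule and the recording task. The boundary is indeed extreme. The illustration shows, however, that a much less extreme split would usually pass as well.

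A third is that the pilot makes no definitive comparison and that this is one criterion among several. Both are true. The criterion exists, though, to show whether a later comparison will have data, and the others do not cover this gap.

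A reader might also infer that the criterion simply passes after early drop-out. The documents do not support that. It requires the held-session reading. Losses above 5 of 20 in either arm already fail retention, so 10 losses in total pass only if split five and five. Counting sessions held is also a defensible way to keep data capture separate from attrition.

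**Conclusion.** The concern holds as a point about the arms. At the target size and on its plain reading, the criterion can be met with one arm at 60 of 120 planned sessions, and no other threshold would reveal it. This assumes 20 children per arm, six sessions each, and a percentage taken over all sessions. The pilot remains valid; the weakness is in what this go/no-go test can show.

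The drop-out point is secondary. It depends on counting sessions held and is bounded by retention, with 59.6% of planned sessions as the example at five losses per arm after session 1. It supports reporting the planned-session percentage. It does not support making planned sessions the threshold, which would count attrition twice.

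**What to change.** Restate the criterion as: data are reported from at least 75% of intervention sessions held, in each arm. Sessions held are the suitable denominator because retention is already judged separately in each arm. In addition, report the percentage of planned sessions (six per randomized child) with data, by arm and session number, without a threshold. This second figure would also show sessions missed by children who stay in the study, which a held-session threshold does not count.

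No new data are needed. The cost is a slightly stricter criterion: any result that passes in each arm also passes overall, but not the reverse. For example, 120 and 89 of 120 give 209/240 = 87.1% overall, yet the second arm falls one session short of 90.

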## Methods

A single-center mixed-methods two-arm parallel group pilot randomized controlled trial with blinded assessors will be carried out. Cases will be stratified by three age groups (4;6–7;11; 8;0–11;11 and 12;0–16;0). A wide age-range was chosen for pragmatic reasons. That is, to both aid recruitment and reflect the typical age range treated with both types of intervention. This will also allow us to gather information about the feasibility of the treatment across different ages and use this information to inform the eligibility criteria of the large-scale study. Due to the nature of the U-VBF, therapists and patients will not be blinded to treatment allocation but the limitations of this will be mitigated by the use of an assessor, blinded to group, and evaluators, blinded to both group and treatment time point. Unblinding to the assessor or the evaluator will not be permissible and is considered unnecessary given the clinicians delivering the intervention are not blind to treatment allocation.

### Participants

#### Inclusion criteria

Children managed by the Scottish Cleft Lip and Palate service aged 4;6 to 16 will be identified and recruited when attending SLT clinics at the Royal Hospital for Children in Glasgow. Invitation letters containing the complete study information sheets will be sent to families. Inclusion criteria regarding age and cleft-type are broad to reflect current clinical practice; however, inclusion criteria for type of cleft speech characteristic are narrower to ensure children are likely to benefit from either U-VBF or the control intervention. Children are eligible if they have at least one speech error that would normally be a candidate for articulation intervention. This will be assessed by a researcher SLT who is not involved in the therapy. We aim to recruit 20 children to each arm of the trial. Recruitment will stop once the target number of participants is recruited and within two years from the beginning of the study. No interim analyses will be performed before all data is collected. In summary, the inclusion criteria are: children aged 4;6 to 16, with any oral cleft-type, who have at least one speech error which requires articulation intervention.

#### Exclusion criteria

The exclusion criteria are: an uncorrected bilateral hearing loss of greater than 30 dB (from previous reports), planned surgery within the next three months, or severe language deficit (from previous SLT reports and a receptive vocabulary standard score < 70 on the BPVS-3, [15] ). Children will be allowed to continue all other medical and speech and language interventions (for example interventions targeting language or social interaction goals may be provided by community SLTs) during the trial. We will collect information on any other speech and language interventions received during the trial.

#### Randomization

Following baseline, the children will be randomized by the Glasgow Clinical Trials Unit in a 1:1 ratio, stratified for age. Children randomized to the control arm will be offered U-VBF at the end of the trial if they still present with CSCs which are candidates for U-VBF for ethical integrity and also because previous studies have shown this improves the acceptability of a randomized trial to families [13].

### Eligibility/baseline assessments

We will screen potential participants from case-notes and invite them to attend an initial screening and baseline assessment. The person carrying it out will obtain consent, ensuring the participants and their families have had time to read, understand, and discuss the information about the study, prior to any assessment or procedures. The person carrying out this assessment will not be involved in the therapy. This assessment will be either in person or via video conferencing, with in-person preferred. Screening assessment will comprise the British Picture Vocabulary Test 3 [15] to screen for adequate receptive vocabulary. This test does not require verbal responses or assess speech production, instead participants point to responses. The screening will also include a speech assessment protocol to determine whether patients present with at least one cleft speech characteristic which would be amenable to both U-VBF and the control intervention. This assessment protocol comprises the Diagnostic Evaluation of Articulation and Phonology [16] articulation and phonology subtests and an ultrasound tongue imaging protocol designed in a previous project [11] to identify covert speech errors from consonants at all places of articulation and sentences from the GoS.SP.aSS.’98/ CAPS-A [17] (Appendix 1). Families who opt for the assessment over video-conferencing will complete the same assessments, but the ultrasound tongue imaging protocol will be replaced with an audio-perceptual assessment of the same materials^1^.

There are some limitations that may arise as a result of online video assessment, such as detecting sounds where the articulators are not visible (e.g., /k/ or /g/) or detecting high-frequency sounds (e.g., /s/ or /ʃ/), despite overall good agreement rates reported for online articulation assessments [18]. However, we retain this option for participants to address potential national and local pandemic regulations [19] during which travelling to a university for assessment is not classified as essential travel.

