### Speech target selection

Children with CLP may present with multiple CSCs affecting intelligibility. We intend to select as intervention targets speech sounds which are (1) amenable to treatment with both interventions and (2) likely to have the biggest functional impact on intelligibility, based on the prevalence of the error during assessment and how frequently the target sound occurs in English minimal pairs [20]. Following the screening assessments, we will select wordlists targeting each child’s specific lingual errors from a battery. In English, lingual speech sounds (imageable with ultrasound and amenable to treatment with both interventions) are /t,d,n,r,l,s,z,∫,ʒ,tʃ,dʒ,j,k,ɡ,ŋ/ and all vowels. Children with CLP are more likely to have difficulty with anterior consonants /t,d,s/. Wordlists containing these speech sounds will also form a key outcome measure (see below). Two wordlists per error type will be selected, firstly an “untreated probe” (i.e., the words will not be used in the course of therapy, and this allows us to check for generalization of targets). Secondly a “treated probe”, containing high-frequency and functionally useful words will be used to train speech targets in the course of therapy. The wordlists contain lingual targets in increasingly complex contexts from single syllable words/pseudowords through to multi-syllabic words and sentences. Where the child has more than one error, multiple wordlists will be used; however, only one treatment target (the speech sound with the most errors) will be selected and the other errors will serve as “control segments” (i.e., speech sounds that should not improve during the course of therapy unless maturation is a factor). Wordlists will be analyzed for percentage target consonants correct (PTC). Children must score < 30PTC at baseline to be eligible for the study.

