### Outcome measures

A blinded assessor will collect measures at baseline (-t1: pre-treatment), 2 months post-randomization (t7, to allow for any delays in referral to therapy), and 3 months post-randomization (t8) to see if any benefit is maintained. Assessment will take place in a university clinic or via video-conferencing and will be carried out by a research SLT blinded to group for primary outcome measures and by the treating SLTs for within-session measures (Table 1).

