### Candidate primary outcome measures

The key primary outcome linear measure for change in speech will be percentage target consonants correct (PTC). We will measure this at single sound level (stimulability and in /aCa/ contexts); single word level; and sentence level in treated and untreated wordlists (i.e., probes, see above section on speech target selection). All direct speech measures will be recorded with audio and where possible ultrasound tongue imaging in both groups, allowing us to perform ultrasound analysis of data from both groups.

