### Ultrasound/speech analysis

All of the speech measures at baseline, and follow-up will be recorded with simultaneous ultrasound in both groups by a research SLT blinded to group where possible. Our previous work showed that the addition of ultrasound to transcription increases inter-rater reliability and allows identification of covert (imperceptible to the ear alone) errors [9]. This will allow us both to calculate PTC (the primary outcome measure) with increased reliability and to perform an error analysis. Twenty-five percent of the data will also be rated by two specialist cleft SLTs (not involved in the project) trained in ultrasound-aided transcription. These SLTs will also rate the audio recordings from the within-treatment sessions (t1 to t6 in Table 1), blinded to group.

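### PTC may be scored with ultrasound at clinic visits and by ear alone at video visits, so a child who changes mode can show a change in PTC, or in eligibility, without a change in speech

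*Protocol article*

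**What the plan says.** Three sections of the protocol article allow either visit mode. Design and setting permits screening and the pre- and post-intervention assessments in person or by telehealth. Eligibility/baseline assessments says of the first visit: "This assessment will be either in person or via video conferencing, with in-person preferred". Outcome measures says of baseline, t7 (2 months) and t8 (3 months): "Assessment will take place in a university clinic or via video-conferencing".

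The scoring information differs with the mode. Under video at screening and baseline, "the ultrasound tongue imaging protocol will be replaced with an audio-perceptual assessment of the same materials". For the outcome, Candidate primary outcome measures states: "All direct speech measures will be recorded with audio and where possible ultrasound tongue imaging in both groups". Ultrasound/speech analysis reports earlier work in which "the addition of ultrasound to transcription increases inter-rater reliability and allows identification of covert (imperceptible to the ear alone) errors", and says that this will be used in calculating PTC and in an error analysis.

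Speech target selection makes PTC an entry criterion: "Children must score < 30PTC at baseline to be eligible for the study". No section says whether that score, or the PTC used for change, is ultrasound-aided or by ear when the two differ.

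**The concern.** A change score is interpretable only if both ends are measured in the same way. Here one end may draw on ultrasound and the other on sound alone, and the protocol itself says that ultrasound picks up errors a listener cannot hear. A production counted as wrong in clinic might therefore count as correct on video. A child seen in clinic at baseline and by video at t7 could appear to improve; the reverse order could hide real improvement.

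The protocol also concedes that video is weak for some sounds, including the high-frequency /s/, while Speech target selection says: "Children with CLP are more likely to have difficulty with anterior consonants /t,d,s". The mode difference may therefore fall on common treatment targets.

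Two things are at stake. The first is who enters the trial, because the < 30 rule can mean different things for different families. The second is the description of pre-post PTC change and its spread, in a pilot whose stated aim is to inform a full trial of similar design.

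**Working it through.** The plan states no figure to reproduce. The check has two parts.

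**1. Does the text lead to two scoring methods for one outcome?**
- PTC is the candidate primary outcome and the entry score (Candidate primary outcome measures; Speech target selection).
- In clinic, ultrasound is recorded where possible and contributes to PTC (Ultrasound/speech analysis).
- By video, the screening and baseline ultrasound protocol gives way to an audio-perceptual one (Eligibility/baseline assessments). The extension to t7 and t8 is an inference: video is allowed there too (Outcome measures), and ultrasound is only recorded where possible.
- No section fixes the mode within a child or names the mode for the entry rule.

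So two methods can apply to the same child at different visits.

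**2. How large could the artefact be?** Let *c* be the share of productions heard as correct that ultrasound would re-class as errors. The documents do not give *c*; 5% to 15% is an assumption. Only productions heard as correct can be re-classed, so

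- PTC with ultrasound = PTC by ear × (1 − c)
- artefact from a switch, with unchanged speech = PTC by ear × c
- a child passes in clinic but fails by video if PTC by ear lies from 30 up to, but not including, 30 / (1 − c)

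| c | PTC by ear 28: with ultrasound | Artefact | PTC by ear 60: with ultrasound | Artefact | Upper limit of the discordant entry range |
|---|---|---|---|---|---|
| 5% | 28 × 0.95 = 26.6 | 1.4 | 60 × 0.95 = 57.0 | 3.0 | 30 / 0.95 = 31.6 |
| 10% | 28 × 0.90 = 25.2 | 2.8 | 60 × 0.90 = 54.0 | 6.0 | 30 / 0.90 = 33.3 |
| 15% | 28 × 0.85 = 23.8 | 4.2 | 60 × 0.85 = 51.0 | 9.0 | 30 / 0.85 = 35.3 |

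The value 28 stands for a child near the entry limit whose speech has not changed. The value 60 stands for a child who has improved and then switches mode, for example between t7 and t8. In this model a move from clinic to video adds these points and the reverse subtracts them. At c = 0 there is no artefact.

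**Group level.** Mean shift = net proportion switching × artefact. If 30% switched from clinic to video (an assumption), the shift would be 0.30 × 1.4 = 0.42 to 0.30 × 4.2 = 1.26 points at 28, and 0.30 × 3 = 0.9 to 0.30 × 9 = 2.7 points at 60.

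Bias between arms = difference in net switching × artefact. It is zero if the arms switch equally. With an assumed difference of 20 percentage points it is 0.20 × 1.4 = 0.28 to 0.20 × 4.2 = 0.84 at 28, and 0.20 × 3 = 0.6 to 0.20 × 9 = 1.8 at 60.

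**With one method at every visit**, this artefact is zero. Differences in sound quality between video and clinic recordings remain.

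**The case against.** The strongest reply is that this is a feasibility pilot. PTC is in none of the progression criteria under Objectives, and the protocol rules out definitive comparisons. That stands: the decision whether to proceed does not depend on this point. Nor does the protocol say that a standard deviation of PTC from the pilot will size the full trial, only that the pilot will inform its design.

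Second, Ultrasound/speech analysis ties ultrasound-aided PTC to reliability. It never states that a production that sounds right but images wrong is scored as an error. If it is not, the mode adds noise rather than a systematic shift. That stands as a limit: a switch can produce a change in PTC, but a reader should not infer that it must. Poor sound on video could also blur the direction for an individual child.

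Third, clinic visits are preferred at screening and baseline, the protocol cites good overall agreement for online assessment, baseline precedes randomization, and follow-up assessors are blinded. A reader might infer a biased contrast between arms, but nothing in the protocol predicts unequal switching. A reader might also infer that baseline PTC will come from a rater who knows the time point, because the entry rule needs a score before randomization. The protocol does not say that this score is reused as the outcome baseline.

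These replies do not remove the core problem. The section that admits the limits of video assessment does not link them to change in PTC or to the threshold. A scoring rule for change might be left to an analysis plan, but an entry criterion has to be unambiguous when children are screened.

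**Conclusion.** The point holds as a possible measurement artefact in PTC change and as an ambiguity in the entry rule. Under the assumed re-classing of 5% to 15% of productions heard as correct, a switch is worth about 1.4 to 4.2 points at a PTC by ear of 28 and 3 to 9 points at 60. Children with a PTC by ear from 30 to just under 31.6 (at 5%) or 35.3 (at 15%) would qualify in clinic and not by video.

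These sizes rest on the assumed rate and on covert errors being scored as wrong. It would be tempting to read a re-classing rate of 5% to 15% as a flat 5 to 15 PTC points. That is too large for children at or below the entry limit, because few of their productions are heard as correct in the first place.

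Feasibility conclusions are untouched. The estimates of pre-post change and its variability are what suffer. The remedy is cheap, because audio is planned for every direct speech measure.

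**What to change.** - Record the assessment mode, and whether ultrasound was obtained, at baseline, t7 and t8. Keep the same mode within a child where possible.
- For pre-post change, score an audio-only PTC at all three visits for every child. Use de-identified recordings in random order and evaluators blinded to group and time point, and re-score baseline in that batch.
- Report ultrasound-aided PTC alongside it for children with ultrasound at all three visits.
- State which scoring mode governs the < 30 PTC rule, and reconcile Eligibility/baseline assessments, Speech target selection and Ultrasound/speech analysis accordingly. Which mode that should be is for the investigators to decide. Audio alone, for instance, might exclude children whose errors are covert, which the ultrasound screening is meant to find.

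The cost is protocol wording and the re-scoring of about 40 baseline recordings. Audio-only PTC is likely to be somewhat less reliable than ultrasound-aided PTC, which is why the latter is kept alongside. Differences in sound quality between video and clinic recordings will remain, so results should also be described by mode.
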